#### Sample size

Sample size calculation is based on the minimal significant change in the clinical parameters and in the impact of the osteoarthritis using the WOMAC index [30]. In order to achieve a power of 80% (beta: 0.2) and a significance level (alpha) of 0.05 for a two-tailed comparison, 124 participants will have to be recruited in each group to detect differences equal or higher than 5 units in the Womac index. An estimated standard deviation of 14, a correlation between the first and second measurement of 0.6 and 20% loss to follow-up have been assumed for these calculations. To take into account the randomization by PHCC, we consider a design effect of 1.45 with a mean number of patients per intervention group of 10 and an intraclass correlation coefficient of 0.05 [31]. The required sample size has been estimated at 180 patients per group: 9 primary care teams with 20 patients each will be recruited for each study group. The statistical package GRANMO v7.12 (IMIM, BCN, Spain) was used for sample size calculation.

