#### Statistical analysis

Data will be analyzed on an intention-to-treat basis following CONSORT CLUSTER criteria to avoid bias by incomplete datasets. Missing values will be replaced by multiple imputation methods. The non-response bias will be monitored and evaluated during follow up. According to the distribution of the variables, descriptive analysis will be carried out using the mean (standard deviation), median (interquartile range) or frequency (percentage).

For comparisons within and between the intervention and control groups we will use Student t-tests for independent and paired data, McNemar, Chi-Square, Fisher’s Exact test, analysis of variance and the corresponding non-parametric tests when appropriate.

To evaluate the effectiveness of the intervention between both groups during follow up, the change in the intervention group minus the change in the control group, as well as the standardized effect size (SES) will be calculated. SES will be calculated as the mean difference between both groups divided by the standard deviation of the control group. To detect differences within each group, the difference between the means at baseline and at each follow up time and the effect size or standardized response mean (SRM) following Kazis’method will be calculated [32]. The SRM will be calculated as the mean change divided by the standard deviation of the change. To evaluate SRM and SES we will use Cohen’s rule, which classifies effect size as small (0.2-0.5), medium (0.5-0.8) and large (>0.8).

We examined the effects of intervention over all time points using mixed-effects models on repeated measures.

Multilevel ordered logistic regression will be used for the response variable “physical activity”, in which patients are categorized in three levels: low: <600 METs. min/week; moderate: > = 600 and <1500 METs min/week; high: between 1500 and 3000 METs min/week.

The PHCC will be considered a random effect. The intraclass correlation coefficient will be calculated to determine which percentage of variability in the response is due to the PHCCs. The final models will be adjusted for potential confounders and relevant clinical variables. Interactions and colinearity will be evaluated [33]. Significance level of the model has been set at 5%. The statistical packages SPSS for Windows, v.21 (IBM SPSS Inc., Chicago, IL) and Stata/SE v.12 for Windows (StataCorp. LP, TX) will be used for statistical analysis.

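### Effectiveness is defined as a difference in changes and baseline WOMAC is given no stated role in the models; at the plan's own correlation of 0.6, adjusting for it would cut variance a further 20%

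*Protocol article*

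**What the plan says.** The Statistical analysis section (protocol article, Phase 2) states one between-group measure of effectiveness in the form of a definition: "the change in the intervention group minus the change in the control group", accompanied by a standardized effect size. Within-group change is summarised by a standardized response mean.

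The same section then plans mixed-effects repeated-measures models across all visits, with the primary care centre (PHCC) as a random effect. On covariates it says only this: "The final models will be adjusted for potential confounders and relevant clinical variables". Baseline WOMAC is neither named nor excluded. The section does not say whether baseline enters the model as a covariate or as one of the repeated outcomes, or whether the model or the difference in changes gives the primary estimate.

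The Sample size section assumes "a correlation between the first and second measurement of 0.6". Table 2 shows WOMAC measured at baseline and at every follow-up.

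**The concern.** When baseline and follow-up correlate at less than 1, subtracting the whole baseline value over-corrects for it. Regression on baseline removes the right amount and never has a larger residual variance than the change score. Two things are at stake.

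- **Precision.** The trial has 18 centres and a sample size that just reaches its power target on the plan's own assumptions. A free gain in precision is worth having.
- **Chance imbalance.** Nine centres per arm are randomised, and the Randomization section mentions no stratification or other balancing. Some difference in baseline WOMAC between arms is to be expected, and a change score passes part of it into the estimated effect.

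**Working it through.** **Inputs (Sample size section).** Two-sided alpha 0.05 and 80% power; a target difference of 5 WOMAC points; SD 14; baseline-to-follow-up correlation 0.6; 20% dropout; and, for clustering, "a design effect of 1.45 with a mean number of patients per intervention group of 10 and an intraclass correlation coefficient of 0.05". Recruitment is 9 centres of 20 patients per arm, that is 180; after 20% loss, 144 are analysed per arm.

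**Step 1: reproduce the plan's figure.**
- Change-score variance: 2 × (1 − 0.6) × 14² = 0.8 × 196 = 156.8 (SD 12.52).
- n per group = 2 × 156.8 × (1.960 + 0.842)² / 5² = 98.5, so 99.
- Allowing for 20% loss: 99 / 0.80 = 123.75, so 124, as stated.
- Design effect: 124 × 1.45 = 179.8, so 180, as stated.

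Using the follow-up value alone (variance 196) gives 124 before loss and 155 after it. Since the stated 124 already includes the loss, it rests on the change score.

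**Step 2: the baseline-adjusted variance.**
- (1 − 0.6²) × 196 = 0.64 × 196 = 125.4 (SD 11.20).
- Ratio to the change score: 125.4 / 156.8 = (1 + 0.6) / 2 = 0.80. The variance is 20% lower; equivalently, change scores need 25% more patients for equal precision.
- The cut depends on the correlation: 25% at 0.5 and 15% at 0.7.
- Sample size on this basis: 79, then 99 after loss, then about 144 after the 1.45 design effect, against 99, 124 and 180.

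**Step 3: power for 5 points, 144 analysed per arm.** SE = √(2 × variance × design effect / 144); power = Φ(5/SE − 1.96).

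| Design effect | Change score | Baseline-adjusted |
|---|---|---|
| 1.45 (as stated, 10 per cluster) | SE 1.78, 80% | SE 1.59, 88% |
| 1.75 (16 analysed per centre: 1 + 15 × 0.05) | SE 1.95, 73% | SE 1.75, 82% |
| 1.95 (20 recruited per centre: 1 + 19 × 0.05) | SE 2.06, 68% | SE 1.84, 77% |

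These are normal approximations. A t reference with 16 degrees of freedom lowers both columns; at 1.75 it gives 67% and 77%.

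**Step 4: chance baseline imbalance.**
- SE of the baseline difference with 180 per arm and design effect 1.95: √(2 × 196 × 1.95 / 180) = 2.06 points.
- Share carried into a change-score estimate, with equal SDs at both visits: 1 − 0.6 = 0.4.
- One-SE imbalance: 0.4 × 2.06 = 0.8 points.
- Three-point imbalance: 0.4 × 3 = 1.2 points, or 24% of the 5-point target. The chance of 3 points or more in either direction is 2 × [1 − Φ(3 / 2.06)], about 15%.

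**The case against.** The strongest reply is that the difference in changes stands in a paragraph on effect-size summaries, while the adjusted mixed models that follow may be the real analysis. If those models include baseline WOMAC, or constrain baseline means to be equal, the efficiency is already recovered. How baseline enters a model is often left to a statistical analysis plan, and this is a condensed article.

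Part of this stands. A reader might infer that the plan has decided against baseline adjustment; the text does not say so. But the reply does not remove the point. The only between-group effect measure that is explicitly defined is the less efficient one, and the sample size was built on it. A repeated-measures model with baseline as an unconstrained outcome would give the same difference in changes through its arm-by-time contrast. This is a stated choice that can be improved, not merely a detail left out.

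Three further readings are tempting and not supported:

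- **That change scores make the stated power too high.** They do not. The sample size uses the change-score variance, and at a design effect of 1.45 the 80% target is met. The lower power at 1.75 or 1.95 comes from the cluster size used in the design effect, which is a separate matter.
- **That the estimate is biased.** Over randomisation it is unbiased. The shift in step 4 is conditional on an imbalance having occurred, and one as large as 3 points is possible but not the usual case.
- **That 20% is the share of the available variance reduction that is lost.** It is the further cut relative to the change score. Against follow-up alone (196), the reduction available is 36%; change scores obtain 20 points of it and forgo 16, which is 44% of what is available.

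**Conclusion.** The point holds as one of efficiency and clarity, not of validity. The plan defines and sizes its effect on change scores and states no role for baseline WOMAC in its models. Baseline adjustment would lower the variance by a further 20% at the plan's own correlation, worth about 8 percentage points of power at the stated design effect (80% to 88%) and about 9 at 1.95 (68% to 77%). It would also remove most of the estimate's dependence on chance baseline differences, which is about 0.8 points for a typical imbalance.

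These figures assume SD 14 at every visit, a correlation of 0.6 at every visit, and the same ICC of 0.05 for the change score and the adjusted outcome. The protocol gives one value of each and does not say which outcome the ICC refers to. The imbalance figures further assume that the patient-level correlation also describes differences between centres. The change is advisable; the trial is not invalid without it.

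**What to change.** In the Statistical analysis section:

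- Name the arm contrast from the mixed model as the primary estimate of effectiveness on WOMAC.
- State how baseline enters: either baseline WOMAC as a covariate, or baseline as an outcome with arm means constrained equal.
- Include arm-by-time terms and random effects for PHCC and for patient.
- Apply the same form to each continuous secondary outcome, using its own baseline value.
- Keep the difference in changes, the standardized effect size and the standardized response mean as descriptive summaries.

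The cost is wording only. Baseline WOMAC is already scheduled for every participant, and no extra patients, visits or measurements are needed. The sample size can stay as it is, since the stated calculation does not rely on the gain.

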This study contains the following limitations: (1) the participants are patients in the PHCCs, which could affect the external validity of the results. However, our health system has universal coverage and over 70% of the population attends yearly the PHCCs; (2) patients with knee osteoarthritis present comorbidities and generally visit the PHCC more often; (3) despite the high prevalence of knee osteoarthritis, clinical practice is highly heterogeneous and the clinical guidelines are barely followed. However, the variability in clinical practice should affect equally the intervention and control groups and the multilevel analysis will take into account and quantify this variability.

This study aims to evaluate the effectiveness and cost-effectiveness of a complex intervention conducted in primary care centres through a Health Coaching Programme on patients with knee osteoarthritis, most of whom are over 60 years of age. The improvements on society and on the patients’ quality of life are in accordance with the WHO tenets for active ageing. Consequently, with this intervention we aim to: 1. achieve a significant improvement of health; 2. assist in changing and maintaining healthy lifestyles and improve the clinical management of patients with knee osteoarthritis; 3. promote active ageing; 4. prevent other conditions thanks to lifestyle changes; 5. provide strategies to remain physically active; 6. provide strategies to remain socially active; 7. provide strategies to remain mentally active; 8. if the study shows the cost-effectiveness and cost-utility of the intervention the results could be transferred to the clinical guidelines and implemented in the primary care centres; 9. allow the professionals and the patients to voice their opinions and their experience of the study; 10. maintain healthy lifestyles through asset mapping; 11. inform primary care professionals via Newsletter; 12. disseminate the results in international journals; 13. disseminate the results through a manual for health professionals; 14. disseminate the results to the general public; 15. disseminate the results in national and international meetings.

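### The plan does not say whether the centre random effect covers change over time; read as a plain centre intercept, it gives the change-versus-change test no allowance for clustering

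*Protocol article*

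**What the plan says.** The Statistical analysis section of the protocol article gives the measure of effectiveness as "the change in the intervention group minus the change in the control group", calculated alongside a standardized effect size. A later paragraph states: "We examined the effects of intervention over all time points using mixed-effects models on repeated measures". On clustering it adds that "The PHCC will be considered a random effect" and that "The intraclass correlation coefficient will be calculated to determine which percentage of variability in the response is due to the PHCCs".

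The section does not say whether the centre (PHCC) effect is an intercept only or also varies with time. It names no patient random effect. It does not say whether baseline WOMAC is a response or a covariate, and it does not name the exact test.

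The Sample size section bases 124 per group on an SD of 14 and a correlation of 0.6 between first and second measurement. For clustering it then states: "we consider a design effect of 1.45 with a mean number of patients per intervention group of 10 and an intraclass correlation coefficient of 0.05". The Discussion acknowledges wide variation in clinical practice and answers that "the multilevel analysis will take into account and quantify this variability".

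**The concern.** One centre random effect with one ICC, in a model for repeated measures, is the usual description of a centre random intercept. Such an intercept has the same value at baseline and at every follow-up, so it disappears when a patient's change is taken. If the model also has a patient intercept and the arm effect is tested as an arm-by-time contrast, the standard error rests on within-patient residual variance alone. Patients' changes are then treated as independent within a centre.

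The sample size assumes the opposite, because it inflates a change-based number for clustering. The intervention also makes shared change within a centre plausible: patients are coached in groups and then followed monthly by their own GP and nurse at the centre.

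At stake is the 5% level for the WOMAC result and for the other continuous outcomes measured repeatedly. Centres whose patients happen to improve together could be read as a coaching effect, with confidence intervals that are too narrow.

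**Working it through.** **Inputs from the article.** From Sample size: "a power of 80% (beta: 0.2) and a significance level (alpha) of 0.05 for a two-tailed comparison"; difference 5; SD 14; correlation 0.6; 20% loss; ICC 0.05; 10 patients per centre in the design effect; 9 centres per arm with 20 patients each, hence 20 × 0.8 = 16 after loss. From Data collection: baseline plus four follow-ups.

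**Step 1: reproduce the plan's figure.**
- SD of change = 14 × √(2 × (1 − 0.6)) = 12.52, variance 156.8.
- n = 2 × (1.96 + 0.8416)² × 156.8 / 5² = 98.5, so 99 per group.
- 99 / 0.8 = 123.75, so 124. This matches "124 participants will have to be recruited in each group to detect differences equal or higher than 5 units in the Womac index".
- Design effect = 1 + (10 − 1) × 0.05 = 1.45; 124 × 1.45 = 179.8, so 180.

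The figure reproduces, and the design effect is applied to a number built on the SD of change.

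**Step 2: the cancellation.** Assume y = arm-by-time mean + centre intercept + patient intercept + residual. Follow-up minus baseline removes both intercepts and leaves two residuals. The variance of the arm contrast in change is 4 × s²/n per arm, with no centre term. With s² = 0.4 × 196 = 78.4, the standard error is √(313.6/144) = 1.48 at 16 per centre (n = 144) and √(313.6/180) = 1.32 at 20 per centre (n = 180).

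**Step 3: type I error if the ICC of change is 0.05.** The true variance is larger by DE = 1 + (m − 1) × 0.05. A single contrast rejects with probability 2 × (1 − Φ(1.96/√DE)). A joint test over four follow-ups rejects with probability P(χ² on 4 df > 9.488/DE).

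| Patients per centre | DE | Single contrast | Joint test |
|---|---|---|---|
| 10 | 1.45 | 10.4% | 16.2% |
| 16 | 1.75 | 13.8% | 24.7% |
| 20 | 1.95 | 16.0% | 30.1% |

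Simulation under no effect (18 centres, 5 visits, 4000 runs per setting) gave 13.7% and 15.2% for the single 12-month contrast, and 24.1% and 29.3% for the joint test, at 16 and 20 per centre.

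**Step 4: if 0.05 is a single-visit ICC instead.** Centre variance at one visit is 0.05 × 196 = 9.8. The ICC of change is 2 × 9.8 × (1 − c)/156.8 = 0.125 × (1 − c), where c is the between-visit correlation of centre effects. The article does not give c, so it is varied here. Single contrast at 16 and 20 per centre:
- c = 1.0: 5% and 5%
- c = 0.9: 7.2% and 7.8%
- c = 0.8: 9.5% and 10.7%
- c = 0.6: 13.8% and 16.0% (the same as Step 3)
- c = 0: 24.8% and 28.6%

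**Step 5: alternatives, by simulation.**
- Centre as the only random effect, no patient term, ICC 0.05 on change: the 12-month change test rejects 2-3%, so it is conservative.
- 12-month response with baseline as covariate and a centre random effect: 5-7% with a normal reference, 4-5% with t on 16 df.
- Comparison of the 18 centre-mean changes: 4-6% in every scenario.

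**The case against.** The strongest objection is that the article never describes the model at fault. It does not say that the centre effect is an intercept only, and random-effects structure is commonly left to an analysis plan, which is not shown here. The inflated error appears only after adding a patient intercept, which is also unstated, while treating a centre-by-time term as absent. Without the patient term the test is conservative. The change-minus-change measure and the mixed model stand in separate paragraphs, and the final models are to be adjusted for relevant clinical variables, which leaves room for baseline WOMAC as a covariate. In that case the centre effect does not cancel.

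Most of this stands, and it limits the claim. A reader might infer that the plan commits to a test rejecting a true null 14-30% of the time under its own ICC. The documents do not support that. It needs an intercept-only centre term, a patient intercept, an arm-by-time test, an ICC of 0.05 that applies to change, 16 to 20 patients per centre rather than the 10 in the design effect, and, for the upper end, a joint test named nowhere. Nor does the Discussion's remark on heterogeneity contradict the model; it states an intention.

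The objection does not remove the point. The article goes beyond silence: it names the effect measure, the model class, the centre term and the ICC. Read ordinarily, that combination misses 5% if change is clustered as the sample size assumes: too high with a patient intercept, too low without one.

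**Conclusion.** The point holds as a conditional one. The article leaves open whether its centre random effect reaches change over time, and the most natural reading does not protect the change contrast in the way the sample size presumes. Under centre and patient intercepts, an arm-by-time test and an ICC of 0.05 on change, type I error for one contrast is about 14-16% at 16 to 20 patients per centre and 10% at 10 per centre. A joint four-visit test would give about 25-30%, or 16% at 10 per centre. If 0.05 is a single-visit ICC, the single-contrast error is about 5% when centre effects are fully stable over time, 7-8% at a between-visit correlation of 0.9 and 10-11% at 0.8. The article does not settle which of these cases applies, so no single error rate can be attributed to the plan.

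**What to change.** Specify one of two models in the Statistical analysis section:

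- follow-up WOMAC as the response, baseline WOMAC as a covariate, and random effects for centre and patient. If several follow-ups are modelled together and one visit is tested, let the centre effect vary by visit; or
- all visits as responses, with random effects for centre, centre-by-time and patient.

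In either case, test the arm effect against between-centre variation with small-sample degrees of freedom (18 centres − 2 = 16). Keep that reference if the added variance component is estimated at zero. Report the ICC of change as well as the ICC of level.

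This changes the wording and adds at most one variance component; it needs no new patients or data. The cost is somewhat wider confidence intervals. If the ICC of change is 0.05, the standard error of the change contrast grows by √1.75 = 1.32 to √1.95 = 1.40 relative to the intercept-only model. With 18 centres, occasional convergence problems should be expected.

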#### Analyses of the economic evaluation

A descriptive analysis of costs and use of resources will be carried out for each study group and these groups will be compared (Table 2).

The time horizon will be of 12 months. The discount rate will be 3%. The incremental cost-effectiveness ratio will be calculated as the difference in the mean costs between both groups divided by the difference between effects of both groups. Health utilities will be calculated through the WOMAC index adjusted by time. The incremental cost-utility ratio will be calculated dividing the difference in mean total costs in both groups by the differences of QALYs of both groups. Acceptability curves will be calculated to determine if the intervention is cost-effective compared with standard clinical practice. An analysis of sensitivity with different discount rates and costs will be carried out to verify the robustness of results.

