#### Exclusion criteria

The following patients will be excluded: patients with knee osteoarthritis in the Kellgren-Lawrence stages 0 and 4; patients with rheumatoid arthritis, fibromyalgia and other systemic rheumatological conditions; patients on a waiting list for orthoses; patients admitted during the past three months for cardiovascular diseases; patients suffering from Parkinson disease, Paget’s disease, cognitive deterioration, metastatic cancer, severe mental diseases and personality disorders; women pregnant or planning a pregnancy.

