#### Allocation of time

Two hours for the following objectives: presentation of the programme, merge the prior knowledge of participants, motivate them and agree on the conditions of the intervention. The following aspects will be discussed: what is health coaching psychology, who can benefit from health coaching, how it works, how it is implemented, confidentiality and aims of the intervention. The treatment and causes of knee osteoarthritis will be also discussed.Twelve hours for the following objectives: scale up physical activity, improve nutrition and increase strategies for the self-management of pain. The following aspects will be discussed: definition of goals, analysis of the current situation, options, action plan and production of individual guidelines for the self-assessment of goal attainment and for the self-assessment of the action plan.Six hours for the following objectives: follow up of the action plan and assessment of results. The following aspects will be discussed: techniques and strategies to follow through the action plan, review of the action plan, review of the assessment of results, assessment of results and prevention of relapse.

The follow up will take place in the primary care centre of the participant, with their own GP and nurse. The nurse and GP will receive training to sustain motivation and weight control. Specifically, they will be trained on positive feedback, patient empowerment and laser questions with motivation and coaching psychology techniques and evidence based information. The pillars and elements of behaviour change will be the same as in the intensive phase. These individual sessions will be conducted monthly and they will last as much as any other follow up visit.

Compliance in relation to the group sessions will be assessed by registering the number of group sessions attended. To ensure patients’ adherence to the group sessions, they will be able to choose between morning or afternoon sessions. One week prior to the group session, they will receive a phone call to remind them the date, time and place of the session and on the day before they will receive an SMS reminder.

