#### Other variables

The main independent variable is the intervention arm: coaching group intervention or usual care.

Socio-demographic, clinical and cost variables will be recorded. Table 2 shows the study variables and the measurement instruments, validated in Spanish and for primary care.

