**Table 2 Tab2:** **Data collection, information sources and follow-up**

**Variables**					**Data collection**				
					**Baseline**	***Follow up from recruitment**			
**Clinical dependent variables**	**Measurement instrument**	**Type of response**	**Scoring (total and per item)**	**Range**	**Before intensive phase**	**After intensive phase**	**3 months**	**6 months**	**12 months**
Qual ity of Life	WOMAC (Batl le, 1999)	Likert (0=none to 4=very much)	TOTAL=24 17= functional l imitation 5=pain 2= sti ffness	0-96	X	X	X	X	X
Pain	ICOAP (Mai l lafert, 2009)	Likert (0=none to 4=very much)	TOTAL = 11 5= constant pain 6= intermittent pain	0-44	X	X	X	X	X
Weight (in Kg.)*	Scale at the PCC	Quantitative (kg.)	-	0 - ∞	X	X	X	X	X
Physical Activity	IPAQ (Puig, 2012)	Duration + Frequency of Moderate to Intense	TOTAL= 7	0 - 3000 MET	X	X	X	X	X
Physical Activity*	Pedometer	Quantitative	-	0 - ∞					
Nutrition	PREDIMED (Mediterranean Diet Adherence Questionnaire	Dichotomous (YES= 1 point NO= 0 points)	TOTAL = 14 12= frequency of consumption of foods 2= Mediterranean food habits	0-14	X	X	X	X	X
Other Variables									
Socio-demographic									
Age, gender, educational level, work status, number of children	Ad-hoc Questionnaire	Nominal	-	-	-	X			
Clinical				-					
Drug Prescription	Ad-hoc Questionnaire	Nominal	1	-	X	X	X	X	X
Diagnostic tests	Ad-hoc Questionnaire	Nominal	1	-	X				X
Waist Circumference	Ad-hoc Questionnaire	Quantitative (cm.)	1	-	X	X	X	X	X
Height	Ad-hoc Questionnaire	Quantitative (cm.)	1	-	X				X
Comorbidities	Ad-hoc Questionnaire	Nominal	1	-	X	X	X	X	X
Duration of Disease in Years	Ad-hoc Questionnaire	Quantitative (years)	1	-	X				
Duration Knee Osteoarthritis in	Ad-hoc Questionnaire	Quantitative (years)	1	-	X				
Costs-related			-						
Direct Medical			-						
Cost of coaching in osteoarthrosis	Ad-hoc Questionnaire	Quantitative (euros)	-	-	X	X	X	X	X
Cost of visits to the GP	Ad-hoc Questionnaire	Quantitative (euros)	-	-	X	X	X	X	X
Cost of visits to the nurse	Ad-hoc Questionnaire	Quantitative (euros)	-	-	X	X	X	X	X
Cost of visits to the physiotherapist	Ad-hoc Questionnaire	Quantitative (euros)	-	-	X	X	X	X	X
Cost of visits to special ist MD	Ad-hoc Questionnaire	Quantitative (euros)	-	-	X	X	X	X	X
Cost of Medical Tests	Ad-hoc Questionnaire	Quantitative (euros)	-	-	X	X	X	X	X
Cost of Pharmacological	Ad-hoc Questionnaire	Quantitative (euros)	-	-	X	X	X	X	X
Operating Costs of the PCC	Ad-hoc Questionnaire	Quantitative (euros)	-	-	X	X	X	X	X

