Cost of Disposable Medical Equipment	Ad-hoc Questionnaire	Quantitative (euros)	-	-	X	X	X	X	X
Cost of transport (ambulance)	Ad-hoc Questionnaire	Quantitative (euros)	-		X	X	X	X	X
Cost of Home Assistance	Ad-hoc Questionnaire	Quantitative (euros)	-		X	X	X	X	X
Indirect Medical			-						
Costs due to loss of productivity (days of sick leave)	Ad-hoc Questionnaire	Uantitative (euro	-		X	X	X	X	X

* Monthly.

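### Table 2's itemised cost list has no line for hospital admissions, emergency visits or knee surgery, so the incremental cost ratios leave out potentially high-cost care

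*Protocol article*

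**What the plan says.** Under Other variables, the protocol article says: "Socio-demographic, clinical and cost variables will be recorded. Table 2 shows the study variables and the measurement instruments". Analyses of the economic evaluation ties the cost comparison to the same table. It says: "A descriptive analysis of costs and use of resources will be carried out for each study group". The arms are then to be compared, with Table 2 cited for the items. The cost-effectiveness ratio divides the difference in mean cost by the difference in effect. The cost-utility ratio divides the difference in mean total cost by the difference in QALYs. The time horizon is 12 months.

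Table 2 lists the direct medical costs one by one, starting with "Cost of coaching in osteoarthrosis" and "Cost of visits to the GP". It continues with nurse, physiotherapist and specialist visits, medical tests, drugs, running costs of the centre, disposable equipment, "Cost of transport (ambulance") and home assistance. One indirect line covers sick leave. Every cost line is collected by an ad-hoc questionnaire at baseline, after the intensive phase, and at 3, 6 and 12 months.

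**The concern.** The list is detailed enough to price disposables and ambulance journeys, but it contains no hospital admission, emergency visit or knee operation. A primary-care-only perspective would explain the gap. The article states none, and its own lines for specialist visits, ambulance, home assistance and lost productivity already go outside primary care.

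Cost-effectiveness and cost-utility belong to the main objective. The Abstract, Background and Discussion make possible use in clinical guidelines depend on them. If the arms differ in hospital use in either direction, a cost difference built from this list will not show it fully.

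**Working it through.** **Step 1: check the list line by line.** Table 2 has 11 direct lines and 1 indirect line, 12 in all. The lines that might be thought to cover hospital care do not:

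- Specialist line: covers visits only.
- Operating-cost line: concerns the running of the primary care centre, not surgery.
- Ambulance line: transport only.
- Comorbidities row (clinical section): a nominal variable. It may show a new diagnosis, but not a stay, its length or its cost.
- Data collection section: adds other clinical data from the electronic medical records without saying which.

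Lines for admission, emergency visit or knee surgery: 0 of 12.

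**Step 2: what the omission does to the ratios.** Let C be mean cost per patient from the listed items, H mean cost per patient from the omitted items, and E the mean effect (or QALYs), in the intervention (I) and control (C) arms.

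- Ratio as planned: (C_I − C_C) / (E_I − E_C)
- Ratio with hospital care: [(C_I − C_C) + (H_I − H_C)] / (E_I − E_C)

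The numerator is wrong by H_I − H_C. If the arms have equal hospital cost, the error is zero. If they differ, the sign of the error follows the sign of that difference. The planned sensitivity analysis varies discount rates and costs, so it can reprice recorded items but cannot restore resource use that was never recorded.

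**Step 3: size.** The article has no figure to reproduce for this point, because it gives neither unit costs nor event rates. The only input it supplies is the arm size: 9 centres × 20 patients = 180 (Sample size). The cost per episode is an assumption, EUR 5,000 to 10,000. One extra event in one arm then shifts that arm's mean cost by:

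- 5,000 / 180 = EUR 27.8 per patient
- 10,000 / 180 = EUR 55.6 per patient

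A wider illustration, also assumed: EUR 3,000 to 10,000 per episode, and a difference between arms of 1 to 5 percentage points over 12 months.

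- Low end: 3,000 × 0.01 = EUR 30 per patient
- High end: 10,000 × 0.05 = EUR 500 per patient

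For scale, the Background quotes EUR 1,502 per patient per year for osteoarthritis. The range is 30 / 1,502 = 2% to 500 / 1,502 = 33% of that figure. This shows scale only. The proper comparator is the cost difference between arms, which the article does not give.

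**The case against.** The article is a condensed protocol, and the full questionnaire may ask about hospital care. What an article leaves to a fuller document is no fault. That does not remove this point: the article fixes the list, presents it as the study variables and ties the cost analysis to it. The fault lies in a list that is given.

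Three stronger readings are tempting, and the documents do not support them.

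- **That serious events go uncounted.** A reader might connect the exclusion of "patients admitted during the past three months for cardiovascular diseases" with a programme meant to "scale up physical activity, improve nutrition and increase strategies for the self-management of pain", and conclude that the trial neglects safety. But the article gives no reason for that exclusion, and usual care in the control group also includes exercise advice. Recording of adverse events may properly sit in the full protocol. Nor would extra rows show the absence of excess events. For example, assume 5% against 8% with an event and 180 per arm. The standard error is √(0.05×0.95/180 + 0.08×0.92/180) ≈ 0.026, so power is only about 20%, before clustering or loss.
- **That the omitted items are the most expensive.** No unit costs or frequencies are given. Stage 4 disease is excluded and the horizon is 12 months, so frequent knee surgery cannot be assumed. Potentially high-cost is as far as one can go.
- **That a programme which causes or prevents admissions would look the same as one that does neither.** Specialist visits, tests, drugs, ambulance, home assistance and sick leave are all costed and would partly reflect an admission.

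It also stands that the comparison is biased only if the arms differ in the omitted items.

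**Conclusion.** The point holds as a gap in the cost list. Followed as written, the incremental cost-effectiveness and cost-utility ratios exclude hospital admissions, emergency visits and knee surgery, while the article calls the cost a total and states no perspective that would justify leaving them out. Differences between arms in hospital use would be missed or only partly reflected.

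Direction and size are unknown. About EUR 28 to 56 per patient for each extra event rests wholly on the assumed EUR 5,000 to 10,000 per episode; the EUR 30 to 500 range also assumes event-rate differences. The line count takes Table 2 as it reads in the published text. The WOMAC analysis is not affected, and no conclusion about patient safety follows.

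**What to change.** Add three items to the resource-use list in Table 2, for both arms and at the existing visits: hospital admissions (date, main reason, days), emergency visits, and knee surgery. Take them from the electronic medical records that the Data collection section already uses and from the interview at each visit, and include their cost in total direct medical cost. If hospital care is left out on purpose, state that perspective and limit the cost-effectiveness conclusion to it.

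The cost is a few more extraction fields and unit costs, with no added visit. Two cautions apply.

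- A few skewed, high-cost events will widen the interval for the cost difference.
- The GPs and nurses who extract the records know the allocation, and intervention patients also have monthly sessions with them. The article does not say that primary care records hold hospital episodes completely. Asking the same fixed questions in both arms at the shared assessment visits guards against unequal ascertainment.
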